### Outcomes

#### Primary outcome measure

The primary outcome measure is the VAS before and after every treatment, after 6 weeks, 3 months and 6 months. The VAS has shown to be a valid and reliable outcome measure [38–41].

The VAS tries to assess a person’s pain intensity level. The patient is asked to place a mark on a 100-mm long line with the question ‘how much pain do you have at this moment’. The beginning of the line illustrates ‘no pain’ the end of the line ‘extreme pain’. To extract the data the researcher measures the distance in millimeters between ‘no pain’ and the mark set by the participant.

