### Statistical methods

#### Number of test subjects

The sample size was calculated with the formula:$$ \mathrm{n} = \mathrm{f}\left(\upalpha, \upbeta /2\right)*2*{\upalpha}^2/{\mathrm{d}}^2 $$

Therefore: 2 × [(1.96 + 0.842)^2^ × 15^2^]/12^2^ = 24.53 [60]

The significance level alpha was chosen at 5 % and the power of 80 %.

From the literature, an expected standard deviation of 15 mm of a VAS can be determined [19]. For the expected mean difference the minimal clinically significant difference (12 mm) on the VAS was determined [61]. To be able to accomplish all needed participants, 2 patients per group will be added addressing possible withdrawals, missing data, and losses to follow up [62]. Therefore, a total of 54 patients will be recruited (27 per arm).

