### Statistical analyzes

Descriptive statistics will be used to illustrate the empirical data and research population. The Shapiro-Wilk test will be used to assess whether all the variables are normally distributed. If the data is normally distributed the changes of VAS will be analyzed using analysis of variance (ANOVA) (repeated measures) to explore possible significant interaction (group x time) effects (α[1]0.05). Secondary outcome variables will be compared using the Wilcoxon test for matched pairs including confidence intervals. Participants will be sub-grouped into acute and chronic to compare the outcomes. To analyze the outcome of the PGIC, patients will be split into 2 groups (dichotomized): improved (6 and 7) and not improved (1 to 5). With the help of logistic regression, the predicted probability of the outcome will be assessed using the PGIC as dependent variables (improved/not improved). Independent variables will be age, sex, expectations, manipulation and duration of complaints. Missing data will be analyzed using an intention-to-treat method. The data will be collected, stored and analyzed in the IBM-SPSS 22 (PASW, Chicago, IL, USA) statistics program.

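### Intention-to-treat is named as the missing-data method, but it is not one; unless a method is added, the repeated-measures ANOVA defaults to complete cases

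*Protocol article*

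**What the plan says.** Under Primary outcome measure, the article states: "The primary outcome measure is the VAS before and after every treatment, after 6 weeks, 3 months and 6 months". The Design section sets three treatment sessions.

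Under Statistical analyzes, provided the data are normally distributed, "the changes of VAS will be analyzed using analysis of variance (ANOVA) (repeated measures") with interest in the group x time interaction. The same paragraph gives the sole missing-data rule, "Missing data will be analyzed using an intention-to-treat method", and names SPSS 22 as the software. No imputation, likelihood-based model or complete-case rule is mentioned.

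Under Number of test subjects, "2 patients per group will be added addressing possible withdrawals, missing data, and losses to follow up", which leads to "a total of 54 patients will be recruited (27 per arm"). No expected rate of drop-out or missing readings is given.

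**The concern.** The article chose to state a missing-data rule, and the rule cannot do what it is said to do. Intention-to-treat defines the analysis population and the arm to which each patient belongs. It leaves open what happens to an empty VAS field.

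The named procedure then settles the matter by default. Classical repeated-measures ANOVA works on complete rows (a property of the method, not something the article says), so one missing reading removes the patient. A patient who completes the three sessions but does not return the 6-month form would lose all eight earlier readings, although the study aim covers short-term as well as long-term effects. If those who stop responding differ in pain or in satisfaction with a technique they could recognise, the patients left no longer form the randomised comparison.

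If an imputation was intended, its choice matters too. Carrying the last value forward, for instance, could place a rating of current pain taken just after a manipulation in the 6-month slot.

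**Working it through.** **1. The plan's own sample size.** Inputs from Number of test subjects: two-sided alpha 0.05 (the formula uses 1.96), power 80%, SD 15 mm, difference 12 mm.

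n per arm = 2 × (1.96 + 0.842)² × 15² / 12² = 24.53, rounded up to 25. Adding 2 gives 27 per arm, 54 in total. The stated figures reproduce.

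**2. Number of readings.** 3 sessions × 2 (before and after) + 3 follow-ups = 9 per patient. The first is the baseline, so 8 are post-baseline.

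**3. What the allowance covers under complete-case deletion.** An expected 25 complete patients per arm remain only while the share with any missing VAS is at most 1 − 25/27 = 2/27 = 7.4%. The article gives no rate per reading, so the following are assumed patterns:
- Independent missingness over all nine readings: 1 − (25/27)^(1/9) = 0.85% per reading.
- Baseline always present, independent missingness over the other eight: 1 − (25/27)^(1/8) = 0.96% per reading.
- Gaps only at the three follow-ups, independent: 1 − (25/27)^(1/3) = 2.5% per visit.
- Whole patients lost: 7.4% of patients.

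**4. Power at assumed shares of incomplete patients.** Normal approximation for the protocol's own comparison of two means: power = Φ(12 / (15 × √(2/n)) − 1.96), with n = 27 × (1 − share).

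| Share with any missing VAS (assumed) | Expected complete per arm | Power |
|---|---|---|
| 0% | 27 | 83.6% |
| 5% | 25.7 | 81.7% |
| 7.4% | 25 | 80.7% |
| 10% | 24.3 | 79.6% |
| 20% | 21.6 | 74.8% |

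Exact t-test values are slightly lower throughout: 82.2% at 27 per arm and 79.2% at 25.

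**5. The same by missing rate (assumed).** At 2% independent missingness over nine readings, 0.98⁹ = 83.4% of patients are complete, or 22.5 per arm (power 76.6%). At 5%, 63.0% are complete, or 17.0 per arm (64.6%). If only the three follow-ups are affected, 2% per visit leaves 25.4 per arm (81.4%) and 5% leaves 23.1 (77.7%).

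**6. Limit of the calculation.** Steps 4 and 5 concern two means at one time point. The group x time test would need correlations between readings and an assumed pattern of effect over time. The article gives neither, so the power of that test, with or without missing data, cannot be derived.

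**The case against.** The case for the plan is that the sentence is loosely worded and no more. The article never mentions complete cases or exclusion. The phrase may be shorthand for an imputation that keeps every randomised patient and then feeds the ANOVA. The article does not fix which time points enter the ANOVA, and it separates short-term from long-term outcomes, so fewer-level analyses are possible. The ANOVA also depends on a normality check. The allowance is expressly for missing data, and no rate shows it to be too small. Six of the nine readings are taken at treatment sessions four days apart, where gaps are least likely, so independence over nine readings is the pessimistic end. The method and its details would normally sit in a statistical analysis plan.

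Much of this stands. A reader might infer that the protocol prescribes a complete-case analysis and contradicts itself outright. The text does not support that: complete cases are what the named procedure falls back on, not a stated rule. A reader might also infer that two per arm is shown to be too few and the trial underpowered. That is not supported either: up to 7.4% of patients with any gap is covered in expectation, 5% whole-patient drop-out lies within that, and 10% costs about one percentage point against 25 per arm. Nor is all the lost power due to ANOVA, since no model fully recovers readings that were never taken.

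One part of this case fails. Leaving detail to an analysis plan would be acceptable, but this sentence gives an answer, and the answer is of the wrong kind. Reading it as imputation means supplying a method that the article does not name, for the primary outcome.

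**Conclusion.** The point holds in conditional form. The stated rule does not handle missing data. With all nine VAS readings in the ANOVA and no imputation, the analysis defaults to complete cases and excludes randomised patients, against the intention-to-treat aim. The direction and size of any bias cannot be judged from the article; it arises if missingness is related to outcome.

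The cost in precision depends on an unstated rate. The break-even is 7.4% of patients with any missing VAS. Power for the two-mean comparison is about 82%, 80% and 75% at assumed shares of 5%, 10% and 20%. Clustering of gaps within patients pulls towards the mild end, scattered gaps towards the severe end. The main reason to act is the validity of the randomised comparison and the waste of recorded readings; the power loss may turn out small.

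**What to change.** Under Statistical analyzes:
- Replace the repeated-measures ANOVA by a linear mixed model fitted by REML, available in SPSS. Include all randomised patients in their allocated arm and every observed post-baseline VAS reading, with arm, visit, arm x visit, and baseline VAS as a covariate. Baseline should not also be an outcome. State that the model is valid under missing-at-random.
- Add one sensitivity analysis that assumes worse VAS after drop-out, for example by shifting imputed values upwards in steps to 12 mm, the difference used for the sample size.
- Reword the sentence on missing data so that intention-to-treat describes only the analysis population.

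No extra patients or measurements are needed, and the first post-treatment VAS is due at the session where the allocation is opened, so nearly every randomised patient should contribute. The cost is that a covariance structure must be chosen in advance. A fully unstructured matrix over eight visits has 8 × 9 / 2 = 36 parameters for 54 patients, so a simpler fallback should be named. Recruitment was still open when the article was written; the change should be dated and made before outcome data by arm are examined.

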### Ethics and data security

This trial has been approved by the Ethics Committee of the Canton of Zurich (KEK-ZH-number 2012-0248). All patients will be asked to provide written informed consent prior to participating in this study. This trial is registered at Current Controlled Trials (ISRCTN 88585962). The collected data will be locked in a secure cabinet and saved at Balgrist University Hospital for 20 years.

## Discussion

The purpose of this study is to compare treatment outcomes for neck pain patients using manual versus instrument-assisted mechanical manipulation at the thoracic spine. For this aim, a randomized clinical trial is the appropriate study. There are already existing trials and reviews that have investigated the treatment of the thoracic spine in neck pain patients [20, 24–30]. Although there are trials that have compared mechanical and manual manipulations [34, 35], no study has worked with the Impulse iQ® (Neuromechanical Innovations, Chandler, AZ, USA). There are several factors which will support the outcome of the study. These are based on the latest knowledge about the treatment of neck pain. First, patients will receive a treatment using an interval of 4 days between each manipulation. This is recommended in the clinical prediction guideline rules for the use of thoracic manipulations in neck pain patients. Second, we added a home exercise program. It is recommended to combine manipulations of the spine with exercises, to have the strongest benefit for patients with neck pain [8]. Third, all outcome measures that are used (VAS, NDI, EQ-5D-5 L) are valid and reliable and have been often used in research. Fourth, to minimize selection bias, a person not involved in the study conducted the randomization of the participants using a computer program. The outcome of the data sheet was then written on cards and put inside opaque, sequentially numbered and sealed envelopes.

One of the trial’s weaknesses might be regarding blinding. We addressed this issue in different ways. To minimize performance bias, the therapist who is conducting the treatment will be unaware of the treatment method until the manipulation is applied. Additionally, the filled-in questionnaires are put inside a sealed, opaque envelop by the patient. The therapist is unaware of the outcome. When the data is put into the database the therapist will be unaware of the associated participant due to de-personalization/anonymity of the questionnaires. Additionally, the expectations of the patient regarding the new and conventional treatment are retrieved beforehand and taken into consideration during the evaluation of the data.

The results of this study may provide useful information for clinicians and patients in terms of effective therapeutic options for treating neck pain patients without the risk of cervical spine manipulation. The outcomes of the research will be published in a timely manner after the completion of this study**.**

## Trial status

Recruitment of study participants is currently ongoing.

### Consent section

Written informed consent was obtained from the patient(s) for publication of this manuscript and accompanying images. A copy of the written consent is available for review by the Editor-in-Chief of this journal.

## Abbreviations

ANOVA: analysis of variance
APTA: American Physical Therapy Association
CAD: cervical artery dysfunction
EQ-5D-5 L: EuroQol 5 Levels 5 Dimensions
NDI: Neck Disability Index
OMT: orthopedic manual therapy
P/E: physical examination
PGIC: Patients’ Global Impression of Change Scale
VAS: Visual Analogue Pain Rating Scale
